# Protocol for *Get Moving*: a randomised controlled trial to assess the effectiveness of three minimal contact interventions to promote fitness and physical activity in working adults

**DOI:** 10.1186/s12889-015-1654-0

**Published:** 2015-03-27

**Keywords:** Physical activity, Intervention, Internet, Monitoring and feedback, Self-monitoring

## Abstract

**Background:**

Web-based interventions for physical activity offer several advantages over face-to-face, print-and telephone-based interventions and are scalable and potentially cost-effective. Recent reviews of web-based interventions in adults show that they have positive but small effects on physical activity but identify a number of limitations including a reliance on self-report measures of outcome. This trial used an objective measure of physical activity to assess the effectiveness of three minimal contact interventions: 1) A multi-component web-based intervention incorporating objective monitoring and graphical feedback of physical activity; 2) A version of the first intervention that consisted only of objective monitoring plus web-based graphical feedback; and 3) Self-monitoring of physical activity using a paper diary.

**Methods/design:**

*Get Moving* is an individually randomised controlled trial with allocation of 488 participants to one of three interventions or to a no-intervention control group. Participants are physically inactive working adults aged 18–65 years. They attended a baseline assessment session at which anthropometric, biological and questionnaire measures were taken and they completed a treadmill exercise test. They then wore a combined movement and heart rate monitor for six days and nights before being randomised to one of the four trial arms. The baseline measures were repeated at the follow-up assessment which took place approximately 12 weeks post-randomisation, conducted by staff blind to group allocation. Participants wore the movement and heart rate monitor for six days and nights before this. The co-primary outcomes are: physical activity energy expenditure measured using individually calibrated combined heart-rate and movement data; and cardiorespiratory fitness measured using a sub-maximal treadmill exercise test.

**Discussion:**

Strengths of the trial include the use of an objective measure of physical activity, a measure of cardiorespiratory fitness, relatively large sample size and the use of robust methods of randomisation, allocation concealment and blinding to outcome assessment. *Get Moving* will contribute to the evidence base on minimal contact interventions for increasing physical activity. The interventions could be implemented in other settings such as primary care.

**Trial registration:**

ISRCTN31844443. Registered 18 June 2010.

## Background

Regular physical activity plays a pivotal role in the prevention and treatment of numerous health related conditions including obesity, depression, anxiety, hypertension, type 2 diabetes, cardiovascular disease, osteoporosis, stroke and breast and colon cancers [1]. Physical inactivity is now recognised as the fourth leading risk factor for global mortality [2], accounting for 6% of all deaths. As such, the World Health Organization (WHO) recommends that adults should do at least 150 minutes (2.5 hours) of moderate-intensity physical activity each week [2]. Furthermore, studies examining the dose–response relationship of physical activity have shown that higher intensity activity (i.e. vigorous-intensity physical activity) improves cardiorespiratory fitness and provides health benefits which are comparable with, and in some cases even greater than, those observed for moderate-intensity activities [3].

Despite the health benefits of physical activity however, insufficient physical activity remains highly prevalent. In the UK more than half of all adults report not meeting recommended levels of physical activity – which is likely to be an optimistic figure given that 95% are not meeting recommended levels when activity is measured objectively [4]. The cost of inactivity to the UK National Health Service (NHS) was estimated at £1.06 billion in 2002, not accounting for the indirect costs resulting from days lost due to sickness absence, premature mortality, private healthcare costs and home care [5]. International reviews conclude that reversal of this physical inactivity pandemic requires public health programmes to encourage increasing activity at societal level, but also interventions to help high risk individuals to increase their levels of physical activity [6].

Previous randomised controlled trials have demonstrated the effectiveness of physical activity promotion among high-risk individuals for reducing the risk of several major non-communicable diseases such as type 2 diabetes [7]. However, these trials have typically been face-to-face interventions – that is, interventions delivered in person – and have been overseen by primary care doctors, physiotherapists, health visitors, health educators, specialist nurses and physical trainers, thereby making them expensive and difficult to implement in real-world settings. Furthermore, greater population health gain will be achieved through shifts in the overall distribution of physical activity as opposed to targeting high-risk groups. The major challenge at this point therefore lies in creating and delivering physical activity interventions which are effective, scalable and affordable to the general adult population. Programmes that deliver an intervention without face-to-face contact may be one way of overcoming these challenges.

In recent years, there has been increasing interest in developing and evaluating web-based interventions for physical activity [8]. These offer several advantages over face-to-face interventions and those based on printed materials and telephone contact, including the potential to reach a large number of people at a relatively low cost, the ability to provide 24-hour access to intervention materials, and the capacity to provide immediate and tailored feedback. Recent reviews of web-based interventions in adults have shown that they have positive but small effects on physical activity. However, they identify a number of methodological limitations of published trials including a reliance on self-report measures of physical activity [9,10].

In the Get Moving trial (*Get Moving*), we are evaluating the effectiveness of a multicomponent web-based intervention developed by Imperative Health (part of AXA ICAS) and designed to support behaviour change in the domains of physical activity and diet. A key feature of the intervention is objective self-monitoring of physical activity. Participants are issued with a tri-axial wrist-worn accelerometer (activity band) from which physical activity data can be wirelessly uploaded to the website where they can view graphs of their progress. Objective monitoring and feedback may facilitate behaviour change in two ways. First, many physically inactive people are not aware of being inactive [11], so feedback may help to motivate them to change. Second, continuous monitoring and feedback enables people to track their progress towards a goal, which is consistent with self-regulation theories of behaviour change such as control theory [12].

Pedometers are commonly used in monitoring and feedback interventions, and there is evidence for the effectiveness of pedometer-based interventions [13,14]. However, few studies to date have evaluated interventions that combine objective monitoring of physical activity with web-based feedback. Richardson and colleagues found a significant increase in physical activity from before to after a six-week intervention in which participants (people with type 2 diabetes) used pedometers with USB ports, uploaded step-count data to a website and received automated feedback [15]. However, this intervention has not been evaluated in a randomized controlled trial. Slootmaker et al. [16] conducted a trial of the PAM (personal activity monitor) system in 102 young office workers. The PAM is a uni-axial accelerometer typically worn on the waist and continuously displays a score showing the cumulative amount of physical activity performed in that day. The information could be uploaded to a website which provided tailored advice and graphically displayed the participant’s progress. The intervention had no significant effect on physical activity or aerobic fitness at three- and eight-month follow-up compared with an information leaflet containing general physical activity recommendations. However, a similar trial in secondary school children found significant effects of the intervention [17]. Physical activity was measured by self-report in both trials.

In the *Get Moving* Trial, in addition to the full multi-component web-based intervention incorporating objective monitoring and graphical feedback of wrist-based physical activity monitoring with an online coaching engine (individualised in response to objective activity data), we include a version of the intervention which consists only of objective monitoring plus web-based graphical feedback. This enables us to test whether objective monitoring and feedback on its own is an effective intervention for physical activity and whether the additional components in the full intervention including the coaching element have any added benefit. The third and final intervention will be self-monitoring of physical activity using a paper-based diary. This technique has been used in numerous physical activity interventions but few studies have attempted to test it in isolation. The review by Fair [18] identified three such trials [19-21] which yielded a non-significant average effect. Self-monitoring using a diary might be expected to facilitate behaviour change through some of the same mechanisms as the objective device-based monitoring with web-based feedback. However, there are potentially important differences between the two approaches that may influence their relative efficacy. For example, the diary method will provide less complete and less quantitative information and therefore cruder feedback about physical activity compared with objective monitoring; the feedback differs in format (diary entries versus activity graph displayed on a webpage); and the monitoring task (writing in the diary versus uploading data from a wearable device) is carried out daily, which may affect engagement with and adherence to the intervention.

### Objectives

The main objective of *Get Moving* is to assess the effectiveness of three minimal contact interventions on objectively measured physical activity energy expenditure (PAEE; a measure of total physical activity) and cardiorespiratory fitness in a general adult population. The interventions will be compared with each other and with a no-intervention control group.

## Methods/Design

### Study design

*Get Moving* is a parallel group, open label, randomised controlled trial with allocation of 488 participants to either no intervention (control group) or to one of three intervention groups: self-monitoring using paper-based diaries (diary group), activity band with web-based feedback (activity band group), or activity band with web-based feedback plus online coaching engine (activity band plus group). The co-primary outcomes are: (1) PAEE measured using individually calibrated combined heart-rate and movement sensing [22,23], and (2) cardiorespiratory fitness measured using heart rate response to a sub-maximal treadmill exercise test. The secondary outcomes are: anthropometric measures (body mass index (BMI), body fat %, weight and waist circumference), blood pressure, plasma vitamin C levels, biochemical measures (HbA_1c_, fructosamine, cholesterol and triglycerides), Short Form 8 (SF-8) health survey questionnaire, theory of planned behaviour (TPB) measures, perceived stress, self-monitoring behaviour and self-reported recent physical activity (RPAQ). Ethical approval was obtained from Cambridge Central NHS Research Ethics Committee (Ref 09/H0308/3). The design of the trial and flow of participants are shown in Figure 1.

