**Table 1 Tab1:** **Measures used in the Get Moving Trial**

**Measure(s)**	**Screening**	**Baseline visit**	**12-week follow-up visit**	**Post 12-week follow-up**

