**Psychological measures**				
Theory of planned behaviour questionnaire		*√*		
Theory of planned behaviour monitoring questionnaire (post-randomisation questionnaire)	Completed two weeks post randomisation			
Conscientiousness questionnaire		*√*		

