**Self-reported health behaviours**				
Recent physical activity (R-PAQ)			*√*	
Functional status (SF-8)		*√*	*√*	
Perceived stress (4-item PSS)		*√*	*√*	
Self-report habit index questionnaire		*√*	*√*	
Gym membership		*√*	*√*	
Smoking status		*√*	*√*	
Vitamin supplement use		*√*	*√*	
Prescribed medications		*√*	*√*	
Frequency of self-weighing		*√*	*√*	

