#### Statistical analysis

Baseline characteristics of the study population will be summarised separately within each randomised group. The co-primary outcomes, PAEE and cardiorespiratory fitness, will each be analysed using an ANCOVA that includes all participants in the group to which they were randomised, regardless of the intervention actually received (Intention-to-Treat analysis). The outcome in the ANCOVA model will be change (follow-up minus baseline) in PAEE (cardiorespiratory fitness), with the baseline value included as a covariate in the model. For each outcome a 3 degrees of freedom test will be performed of the null hypothesis that there is no difference between the 4 randomised groups. The ANCOVA model will also be used to derive estimates of the differences in mean change and 95% confidence intervals for each of the 6 pairwise comparisons: ‘*Diary*’ vs. ‘*Control*’, ‘*Activity Band*’ vs. ‘*Control*’, ‘*Activity Band Plus*’ vs. ‘*Control*’, ‘*Activity Band*’ vs. ‘*Diary*’, ‘*Activity Band Plus*’ vs. ‘*Diary*’ and ‘*Activity Band Plus*’ vs. ‘*Activity Band*’. Where baseline values of the outcome are missing, the missing indicator method will be used to enable these participants to be included in the analysis [40]. An analysis will be performed to check whether adjusting for age, sex and BMI (the randomisation stratifiers) in the ANCOVA model has any impact on the conclusions; if it has no impact, then they will not be included in the model.

For each continuous secondary outcome, the 6 pairwise differences between randomised groups will be estimated, together with 95% confidence intervals, using ANCOVA as described previously. Any continuous endpoints whose distribution is skewed will be log transformed prior to analysis, in which case a ratio of geometric means (and confidence interval) will be reported.

Subgroup analyses by sex and BMI (below/above median value) will be investigated for the 2 co-primary outcomes only.

Degree of use of the intervention will be summarised separately within each intervention group (i.e., the Diary, Activity Band and Activity Band Plus groups). The numbers and types of adverse events within each randomised group will be reported.

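### The change-from-baseline ANCOVA set for continuous secondary outcomes does not fit RPAQ or either theory of planned behaviour scale, because Table 1 gives each a single measurement time

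*Protocol article*

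**What the plan says.** **Outcome list.** In the Protocol article, Study design, the secondary outcomes end with "theory of planned behaviour (TPB) measures, perceived stress, self-monitoring behaviour and self-reported recent physical activity (RPAQ"). The TPB entry is not limited to one instrument. The Psychological measures section describes two TPB questionnaires, one on becoming more active and one on self-monitoring of activity.

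**Analysis rule.** Statistical analysis states: "For each continuous secondary outcome, the 6 pairwise differences between randomised groups will be estimated, together with 95% confidence intervals, using ANCOVA as described previously". The model referred to is defined just before: "The outcome in the ANCOVA model will be change (follow-up minus baseline) in PAEE (cardiorespiratory fitness"). The same sentence then sets the adjustment: "with the baseline value included as a covariate in the model". For absent baselines the section adds: "Where baseline values of the outcome are missing, the missing indicator method will be used to enable these participants to be included in the analysis".

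**Schedule.** Table 1 ("Measures used in the Get Moving Trial") has columns for screening, baseline visit, 12-week visit and after the 12-week visit. The entry "Theory of planned behaviour monitoring questionnaire (post-randomisation questionnaire") is marked as completed two weeks after randomisation, and "Recent physical activity (R-PAQ") has one tick, at 12 weeks.

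**Abstract.** The Methods/design paragraph says in general terms that baseline measures were taken again at follow-up.

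**The concern.** A change score needs two measurements of the same quantity, and adjustment for baseline needs one taken before randomisation. If a listed outcome has only one time point, the analysis promised for it does not exist and something else has to be chosen later. If the only time point precedes randomisation, no analysis can show an intervention effect: a comparison of groups would describe chance baseline imbalance.

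What is at stake is the pre-specification of some secondary results. RPAQ matters most. It is a self-report measure in an open-label trial, and the choice of adjusted or unadjusted comparison should be fixed before the data are analysed.

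**Working it through.** **Step 1. Schedule against model.** Table 1 read row by row for the measures at issue, with one neighbouring row for contrast:

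| Measure | Baseline | After randomisation | Change score possible? |
|---|---|---|---|
| Physical-activity TPB scale | yes | none | no |
| Monitoring TPB scale | none | two weeks | no |
| RPAQ | none | 12 weeks | no |
| Self-monitoring behaviour | none | 12 weeks | no |
| Perceived stress (contrast) | yes | 12 weeks | yes |

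The SF-8 and habit index rows, in the same block as RPAQ, carry ticks at both visits, so the single RPAQ tick does not look like a fault of text extraction. The Post-randomisation questionnaire section says that the two-week form covers determinants of monitoring behaviour. It therefore does not provide a later physical-activity TPB score.

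**Step 2. Does the missing-indicator rule help?** Write the model as Y1 − Y0 = a + group effects + b·Y0 + c·M, where M = 1 if Y0 is missing. If nobody has Y0, the change on the left does not exist for anyone. Suppose the rule is applied mechanically, with a constant k put in for Y0:

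- The left side becomes Y1 − k.
- The design has 6 columns: intercept, three group indicators, the constant baseline and M = 1 throughout.
- The last two are multiples of the intercept or zero, so the rank is 4 of 6.
- The group coefficients equal the differences in mean Y1. A numerical check with 100 per group gave identical values.

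The result is a plain comparison of post-randomisation means, which is a valid analysis but not the change analysis that the plan states. For the physical-activity TPB scale there is no Y1, so nothing can be fitted.

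**Step 3. Precision of a post-randomisation comparison.** The detectable difference at 80% power and two-sided 5% is (1.960 + 0.842) × SD × √(2/n) × √(1 − r²), where r is the correlation between covariate and outcome.

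The formula first reproduces the plan's own figures with n = 100 per group:

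- PAEE unadjusted: 2.802 × 0.076 × 0.1414 = 0.0301 (stated 0.03).
- PAEE adjusted, r = 0.58: 0.0301 × √(1 − 0.3364) = 0.0245 (stated 0.025).
- Fitness, SD 1.0, r = 0.88: 0.396 × √(1 − 0.7744) = 0.188 (stated 0.19).

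For an outcome with no covariate it gives 0.396 SD. With a covariate it gives 0.378 SD at r = 0.3, 0.343 at r = 0.5 and 0.283 at r = 0.7. These r values are assumptions, since the article gives none for these scales or for RPAQ against baseline PAEE.

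**The case against.** **The rule may be loose shorthand.** Change adjusted for baseline and follow-up adjusted for baseline give the same group contrast, and with no baseline at all the fit collapses to post-randomisation means, as step 2 shows. A reader might infer that these measures would drop out of the analysis with no participants usable. The documents do not support that: RPAQ, the monitoring TPB scale and self-monitoring behaviour can be compared validly between randomised groups. The mismatch still stands, because the missing-indicator sentence concerns participants who lack a baseline, not instruments never given at baseline.

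**Self-monitoring behaviour may not be continuous.** Table 1 places it among other questionnaires and single-item questions, and no scale is given. If it is categorical, the ANCOVA sentence does not cover it. This stands, so the point rests on RPAQ and the two TPB scales.

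**Table 1 may be incomplete.** The Abstract's general statement that baseline measures were repeated leaves open that the physical-activity TPB scale was given again at 12 weeks. This also stands, and it is why the request is to reconcile the texts rather than simply to delete the scale. On the other side, the example items in Psychological measures look ahead to the next 12 weeks, which suits a baseline form.

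**Mediation.** A reader might infer that the Discussion's remark on mediation pathways fails. It names no physical-activity TPB construct, and possible mediators measured after randomisation exist: the monitoring TPB scale, self-monitoring behaviour and the habit index. That criticism is not supported.

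**Detail left to the analysis plan.** A condensed article may leave model detail elsewhere. Here, however, it states a rule that conflicts with its own schedule, which is different from leaving detail out.

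**Conclusion.** The point holds in limited form. Three instruments (RPAQ and both TPB scales) certainly lack the pair of measurements that the stated model needs, and a fourth (self-monitoring behaviour) lacks it too if it is continuous. Of the four, only the physical-activity TPB scale cannot be an outcome as scheduled. For the other three the fault lies in the stated model, not in their use as outcomes.

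The other listed secondary outcomes, such as weight, waist, body fat, blood pressure, the blood measures, SF-8 and perceived stress, are ticked at both visits; BMI needs only the baseline height. The co-primary analyses and the sample size are unaffected. The conclusion assumes that the Table 1 ticks are in the right columns and that RPAQ and the TPB scales are analysed as continuous scores.

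**What to change.** 1. Reconcile the Abstract, the outcome list in Study design, Table 1 and Statistical analysis.
2. In Statistical analysis, state that RPAQ, the monitoring TPB scale and self-monitoring behaviour are compared between groups on their single post-randomisation value, and say whether self-monitoring behaviour is continuous.
3. Adjust RPAQ for baseline objective PAEE. The covariate is at hand, because randomisation took place only after the returned monitor data had been checked (at least 35 hours).
4. If the physical-activity TPB scale or RPAQ was in fact taken at both visits, correct Table 1 and keep the ANCOVA for it. If the physical-activity TPB scale was taken only at baseline, remove it from the secondary outcomes and describe it as a baseline variable.

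The cost is a few sentences and possibly one or two table entries. No new data are needed. The changes should be made before the secondary outcomes are analysed.

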**Figure 1 Fig1:**
[figure not shown]
